##### Analysis Procedures

Following guidelines for clinical trial analysis, all primary analyses will be intention-to-treat analyses and missing data will be handled using multiple imputations.

##### Mixed-Effect Models

The principal strategy to examine primary and secondary outcomes over time between the Suubi-Mhealth group and the control group will be the use of linear mixed models and generalized linear mixed models, including a random intercept to allow for the correlation of within-participant measurements over time. Models will include the fixed effects of the intervention group (Suubi-Mhealth vs control), time, and group-by-time interaction. Effect sizes and 95% CIs will be reported.

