## Methods

### Study Overview

The overall goal of this study is to develop a mHealth intervention (Suubi-Mhealth) for use among Ugandan youths with comorbid HIV and depression, taking into account their unique contextual, cultural, and developmental needs. In phase 1 of the study, we will conduct 4 focus group discussions, each with 6-8 youths and 2 focus group discussions with health care providers, for feedback on the proposed intervention content and methods. Based on the results from focus group discussions, we will recruit 30 youths to engage with the Suubi-Mhealth app to explore its feasibility and acceptability so as to inform subsequent refinement for the larger phase of this project. In phase 2, a total of 200 youth from 10 health clinics will be recruited, and randomly assigned to either the Suubi-Mhealth condition or waitlist control condition (5 clinics with 100 youths per condition), to pilot-test the preliminary impact of the intervention on reducing depression and improving ART adherence, mental health functioning, quality of life, and lowering HIV stigma. Upon intervention condition, we will qualitatively examine participants’ intervention experiences, as well as barriers and facilitators for integrating Suubi-Mhealth into health care settings. The hypothesized relationships are provided in Figure 1 below.

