### Description of the Study Conditions

In phase 2 of the study, participants will be randomized to 2 conditions (100 youths per condition): a waitlist control condition or the Suubi-Mhealth condition, as detailed below.

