##### Structural Equation Models

We will use mediation analysis to examine whether depression symptoms mediate ART adherence. We will test for mediation using structural equation models with CIs derived from bootstrapping of indirect and total effects. By applying mediation analyses, we will be simultaneously testing whether the intervention engages the targets and whether intervention-induced changes in targets are associated with clinical benefit. Models will account for baseline scores. For sensitivity analyses, we will use a per-protocol approach to address noncompliance by only including participants who completed the study according to the protocol.

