##### Sample Size and Power

The primary outcome in aim 1 is whether depression decreases between baseline and postintervention initiation. This is calculated from the depression score change between these 2 time points and categorized as yes versus no. The intracluster correlation for clinics is assumed to be 0.093 and the rate of depression decrease in the control group is 5% [95]. Given our total sample (N=200, 100 youths per condition, 5 clinics per condition), we expect to achieve at least 80% power to detect a rate difference of depression decrease when the rate of depression decrease in the intervention group is 40% and the 2-sided significance level of the test is .05.

##### Milestone for Phase 2, Aim 1

Successful completion of a parallel-group RCT to test the feasibility, acceptability, and preliminary efficacy of Suubi-Mhealth*.* Participants will not experience any adverse events. Participants will have engaged with Suubi-Mhealth daily for 2 months and engaged with at least 75% or more of the modules.

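### Five whole clinics per arm and a clinic ICC of 0.093 are assumed, but the principal model has no clinic term: if that ICC applies to change in depression, a nominal 5% test of the primary outcome rejects a true null about 24% of the time

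*Protocol article*

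**What the plan says.** The Study Overview describes 200 youths from 10 clinics, "randomly assigned to either the Suubi-Mhealth condition or waitlist control condition (5 clinics with 100 youths per condition"). Sample Size and Power repeats the layout ("N=200, 100 youths per condition, 5 clinics per condition") and adds: "The intracluster correlation for clinics is assumed to be 0.093". That section defines the primary outcome as whether depression decreases: "This is calculated from the depression score change between these 2 time points and categorized as yes versus no".

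The Mixed-Effect Models section gives the principal strategy for primary and secondary outcomes. It uses linear and generalized linear mixed models, "including a random intercept to allow for the correlation of within-participant measurements over time", with fixed effects for group, time and their interaction. Clinic is in neither the random nor the fixed part. The article mentions no cluster-robust variance and no correction for a small number of clusters.

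On the unit of allocation the article is not consistent. Description of the Study Conditions says "participants will be randomized to 2 conditions (100 youths per condition". The Waitlist Control Condition section and the Phase 2, Aim 1 overview likewise speak of participants being randomised.

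**The concern.** If each clinic sits wholly in one arm, the difference between arms carries the clinic-to-clinic variation of only five clinics on each side. A participant intercept handles repeated measures on one youth. It does nothing for the correlation between youths of the same clinic, so the model treats 200 youths as independent when there are 10 allocated units. The yes/no primary outcome has one value per youth, so there the participant intercept offers no protection at all.

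The sample-size section allows for this correlation and the stated analysis does not. At stake is the trial's efficacy signal. The article plans a two-sided .05 test and promises effect sizes with 95% CIs. If clinic is ignored, those intervals can be too narrow and the false-positive rate too high.

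**Working it through.** **Inputs.** From Sample Size and Power: 100 youths and 5 clinics per condition, ICC 0.093, rates 5% (control) and 40% (intervention), two-sided .05, power at least 80%. Cluster size is 100/5 = 20, assuming equal clinics. The article gives no attrition figure, so none is applied.

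**1. Does the stated power allow for clinics?**
- Design effect = 1 + (20 − 1) × 0.093 = 2.767. Effective n per arm = 100/2.767 = 36.1.
- Unpooled SE = √[(0.05 × 0.95 + 0.40 × 0.60)/36.1] = 0.089, and 0.35/0.089 ≈ 3.92.
- Power is 97.5% (unpooled z) or 96.1% (pooled z). With a t test on 8 df it is 92.8% (unpooled) or 87.6% (pooled). A simulated clinic-level t test gives 92.7%.

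Every variant satisfies the stated lower bound of 80%, so the sample size does allow for clinic correlation.

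**2. Error rate if the analysis leaves clinic out.**
- SEs are too small by a factor of √2.767 = 1.663.
- Actual type I error = 2 × [1 − Φ(1.96/1.663)] = 2 × [1 − Φ(1.178)] = 23.9%.
- Simulation (40,000 trials, 10 clinics of 20): 24.0% for a continuous change score. For a yes/no outcome it is 22.2%, 24.1% and 24.4% at true rates of 5%, 22.5% and 40%.
- A t test on clinic-level summaries (8 df), same simulations: 4.9% continuous; 3.1% to 5.1% yes/no.

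**3. Sensitivity of the 23.9%.**
- ICC 0.05: design effect 1.95, error 16.0%. ICC 0.02: 1.38, 9.5%. ICC 0.01: 1.19, 7.2%.
- With 18 or 16 youths analysed per clinic at ICC 0.093: 22.2% or 20.5%.

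**4. The repeated-measures model.** This simulation used 8,000 trials per row, four visits and a participant intercept only. The variance components are illustrative and are not taken from the article.

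| Clinic effect | Group-by-time, one visit vs baseline | Group-by-time, joint 3-df test | Group difference at one visit |
|---|---|---|---|
| Constant over time (variances: clinic 0.093, participant 0.407, residual 0.5) | 4.9% | 5.1% | 24.4% |
| Half constant, half varying by visit (0.0465 each; participant 0.407, residual 0.5) | 22.8% | 40.3% | 24.7% |
| Varying by visit only (clinic-by-visit 0.0513, participant 0.45, residual 0.5; ICC of change 0.093) | 24.2% | 41.4% | 16.8% |

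In the last row the clinic-by-visit variance is 0.093 × 0.5/(1 − 0.093) = 0.0513, which makes the ICC of a change score 0.093.

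A constant clinic effect cancels from a comparison of changes. Clinic variation in change does not.

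**The case against.** **One error rate for the whole plan.** A reader might infer that every 5% test in this trial runs at 22% to 24%. The documents do not support that. The model centres on group, time and group-by-time, and no contrast is named as primary. As the table shows, the group-by-time rate can be nominal, about 24%, or above 40%, depending on how clinic effects behave over time.

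**What 0.093 refers to.** The article does not say that the ICC is for change. It follows directly on the definition of the change-based outcome, so that reading is natural, but it is an inference. If 0.093 is an ICC at a single time point, the ICC for change is unknown.

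**Whether clinics are randomised.** The article never says so outright, and three sections say participants are. Under individual randomisation within clinics this inflation would not arise. But then five clinics per condition would make no sense, and there would be no reason to size the trial with a clinic ICC in this layout. Allocation by clinic is the better reading, and the wording needs reconciling either way.

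**A condensed article.** The App Engagement and Usability section refers back to covariance structures that the article does not describe, so the modelling text may have been shortened. This disposes of a wider complaint. A reader might count it as an error that clinic is missing from the imputation and from the mediation analysis ("We will test for mediation using structural equation models with CIs derived from bootstrapping of indirect and total effects"). Those passages state nothing wrong, and such detail is commonly left to a fuller document. The principal model is different: the article states its random effect, the purpose of that effect and its fixed effects. Followed as written, the model omits clinic.

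**It is a pilot.** True, but it still specifies a .05 test and 95% CIs, and its milestone includes preliminary efficacy.

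**Conclusion.** The mismatch is real and should be corrected before analysis: the design and sample size assume clinic correlation, and the stated principal model does not account for it.

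For the primary outcome, true type I error is about 24% at a nominal two-sided 5%. This assumes that whole clinics are allocated, that about 20 youths per clinic are analysed, and that 0.093 is the ICC for change in depression. At ICC 0.02 to 0.05 it would be about 9.5% to 16%. If clinic effects are constant over time, group-by-time tests stay near 5%, while a group difference at one visit is still inflated.

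Two stronger readings go too far. The first is that an ineffective app would be declared beneficial in one trial in four. The 24% is two-sided, so about half of it, 12%, would favour the app. The second is that secondary outcomes suffer to the same degree. They share the model and so the weakness, but with no ICC given for them the size cannot be stated.

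**What to change.** 1. State that the clinic is the unit of allocation. Bring Description of the Study Conditions, Waitlist Control Condition and the Phase 2, Aim 1 overview into line with the Study Overview and Sample Size and Power. If youths are in fact randomised individually within clinics, the latter two sections need correcting instead.
2. Account for clinic in the arm comparisons, in one of two ways:
   - add a clinic random effect that covers clinic variation in change, for example clinic and clinic-by-visit, with a prespecified simplification if the fit is singular, tested with a small-sample correction (Kenward-Roger or Satterthwaite, about 8 df); or
   - compare the 10 clinic-level summaries of change (mean change, or proportion with a decrease) by a t test on 8 df. With so few clinics this is the sturdier choice, and it kept the error at or below about 5% in the simulations above.
3. Name the contrast that carries the primary test, since the effect of leaving clinic out depends on it.

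**Cost.** This changes analysis wording only and needs no new data or participants. Intervals become wider. At ICC 0.093 for change the factor is about 1.663 × 2.306/1.960 = 1.96, where 2.306 is the two-sided 5% critical value of t on 8 df, so they roughly double. Power for 5% versus 40% stays at about 88% to 93% with 20 youths per clinic, above the stated 80%.

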##### Moderation Analysis

First, we will provide descriptive statistics on engagement (session duration, number of modules viewed) and usability scores. We will then use moderation analysis to examine whether Suubi-Mhealth engagement and usability scores moderate the effect of the interventions on our primary and secondary outcomes of interest (ie, depression, ART adherence, psychological distress, overall quality of life, shame, and HIV stigma).

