#### Waitlist Control Condition

A waitlist control condition method will be used [70]. Participants will be randomly assigned to a waitlist and will receive the Suubi-Mhealth intervention after the active treatment group. In addition, participants will receive a smartphone without the Suubi-Mhealth app at the same time as the intervention group.

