### Quantitative Assessments

Quantitative assessments will be administered as follows. In phase 1, interviewer-administered quantitative assessments will be collected at 2 months post intervention to examine the usability characteristics and engagement with Suubi-Mhealth. To assess usability characteristics, we will administer a modified version of the 19-item USE (Usefulness, Satisfaction, and Ease of Use) questionnaire to measure usability characteristics of Suubi-Mhealth [76,77]. The USE will ask participants to rate the ease of use and learning (ie, efficiency), usefulness (ie, technical effectiveness), and likability (ie, satisfaction) of Suubi-Mhealth on a 7-point Likert scale (with 1= strongly disagree and 7= strongly agree).

To assess engagement with Suubi-Mhealth, automatically captured data within the app platform will be used to measure app engagement for each participant, including (1) the number of modules completed, (2) the number of messages sent, (3) the number of times self-monitoring and goal-setting features used, (4) the number of times logged into the app, (5) the time spent in the app once logged in, and (6) the time difference between app log-ins.

In phase 2, assessments will be completed at baseline and at 1, 2, and 6 months post intervention to evaluate whether participants’ ART adherence and self-reports on symptoms of depression, mental health functioning and physical health, and quality of life and stigma improve with access to Suubi-Mhealth and whether improvements remain consistent over time. The measures to be used are provided in Table 1 below.

**Table 1 table1:** Phase 2 assessment measures.

Variable	Measures
Demographics	Sociodemographic questionnaire
Depressive symptoms	Patient Health Questionnaire-9 (PHQ-9) [61] and Brief Symptom Index (BSI) [78]
Physical health	The Medical Outcomes Study HIV Health Survey (MOS-HIV) [79]
Quality of life	Pediatric Quality of Life Inventory (PedsQL 4.0) [80,81]
HIV shame	Shame questionnaire [82,83]
HIV stigma	Berger HIV Stigma Scale [84]
Social support	The Multidimensional Scale of Perceived Social Support [85] and Social Support Behavior Scale (SS-B) [86]
ART^a^ adherence	Viral load; self-reports [87]
Intervention feedback	In-depth interviews

^a^ART: antiretroviral therapy.

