#### Phase 2, Aim 1: to Pilot-Test the Preliminary Impact of Suubi-Mhealth

##### Overview

During phase 2, participants will be randomized to the intervention condition to engage with the Suubi-Mhealth app or the control condition (waitlist control group) to receive the app after the active intervention period. Assessments will be completed at baseline and at 1 month, 2 months, and 6 months post intervention to evaluate whether participants’ self-reports on symptoms of depression, ART adherence, mental health functioning, quality of life, and stigma improve with access to Suubi-Mhealth and whether improvements remain consistent over time.

Participants will also complete the USE measure to assess acceptability and usability, as well as in-depth interviews to explore their experiences with the intervention.

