##### App Engagement and Usability

Basic descriptive statistics will be reported for Suubi-Mhealth engagement (session duration and number of modules viewed), as well as app usability scores (USE scores and subscales of efficiency, technical effectiveness, and likability). To determine the relationships between app usability and engagement, we will use linear regression models with an index of engagement (derived from principal components analysis using the above raw metrics of engagement) as the dependent variable and overall usability score as the primary predictor of interest. Demographics associated with both the usability scores and the index of engagement will be included as covariates in the model. In a separate model, we will include each usability subscale (efficiency, technical effectiveness, and satisfaction) rather than the overall usability score in order to explore which subscale might be most predictive of engagement with the mobile app-based tool. In addition, linear mixed models will be used to investigate the association between the intervention engagement index with the primary outcomes over time. Covariance structures for the models will be selected as described above. Effect sizes and 95% CIs will be reported.

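### App engagement and usability cannot serve as moderators of the arm effect: they arise after randomisation and controls have no values during the comparison (secondary analysis; should be fixed)

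*Protocol article*

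**What the plan says.** The Moderation Analysis section first describes the candidate moderators: "we will provide descriptive statistics on engagement (session duration, number of modules viewed) and usability scores". It then says the analysis will "examine whether Suubi-Mhealth engagement and usability scores moderate the effect of the interventions on our primary and secondary outcomes of interest", and lists six outcomes: depression, ART adherence, psychological distress, quality of life, shame and HIV stigma.

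Other sections show where these variables come from and who can have them:

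- Quantitative Assessments, in its phase 1 part, gives the only description of the data source: "automatically captured data within the app platform will be used to measure app engagement for each participant". Usability is a rating of the app itself: "The USE will ask participants to rate the ease of use and learning (ie, efficiency), usefulness (ie, technical effectiveness), and likability".
- The Phase 2, Aim 1 Overview says "Participants will also complete the USE measure to assess acceptability and usability" and does not name an arm.
- Waitlist Control Condition says of controls: "participants will receive a smartphone without the Suubi-Mhealth app at the same time as the intervention group". The Phase 2, Aim 1 Overview describes "the control condition (waitlist control group) to receive the app after the active intervention period".
- App Engagement and Usability plans a separate model: "linear mixed models will be used to investigate the association between the intervention engagement index with the primary outcomes over time".

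**The concern.** A moderator of a randomised effect must be defined in both arms and must not be affected by assignment. Otherwise one cannot compare the arms at a given level of it. Engagement and usability fail both conditions: they exist only because a youth was given the app, and no control has the app while the arms are being compared.

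An analyst following the section literally would meet a model that cannot be fitted, or would quietly fit a substitute. The natural substitute is the slope of outcome on use among app users. That slope mixes any effect of use with the reasons some youths use an app more than others. The article's Introduction links depression to apathy, forgetfulness and low energy, and it is plausible that these also reduce app use. A slope of this kind, reported as moderation, could look like evidence that the app works better with more use even if it does nothing.

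**Working it through.** The article states no figure for this analysis, so there is none to reproduce. The check concerns identification, followed by an illustration of size.

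**Inputs.** 100 youths per arm and four visits (Sample Size and Power; Phase 2, Aim 1 Overview). Controls have no app during the active period (Waitlist Control Condition). Missing data are handled by multiple imputation (Analysis Procedures). Assumption, not from the article: engagement and outcome each correlate 0.4 with an unmeasured prognostic factor.

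**Model.** Write A = 1 for the app arm and 0 for control, and E for engagement. Moderation of the arm effect is the coefficient b3 in

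Y = b0 + b1·A + b2·E + b3·(A×E).

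**1. E set to 0 in controls.** In the app arm A = 1, so A×E = E. In controls E = 0, so A×E = 0 = E. The two columns agree in all 200 rows. The design has rank 3 of 4, and only b2 + b3 can be estimated. Crossing the four terms with three visit indicators gives 4 × (1 + 3) = 16 columns. Four of them are duplicates, so the rank is 12 of 16.

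**2. E missing in controls, complete cases.** All 100 controls drop out. Then A = 1 throughout, the columns reduce to an intercept and E, and the rank is 2 of 4. Neither the arm effect nor the interaction remains.

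**3. E imputed in controls.** No control has a comparison-period value, so nothing in the data informs how E and Y relate in that arm. In 1,000 simulated trials with no app effect, the mean interaction was 0.16 when E was imputed without the outcome and 0.00 when imputed with it. The imputation model determines the answer.

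**4. Usability.** Zero has no meaning as a rating of an app never used, so option 1 is not available. Options 2 and 3 fail for the same reasons as above.

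**5. What can be estimated.** Dropping the product term leaves A and E, which is full rank. With E = 0 in every control, its slope is the within-app-arm slope of Y on E. With no app effect and the assumed correlations, that slope has expectation 0.4 × 0.4 = 0.16 SD of outcome per SD of engagement. Over 4,000 simulated trials with 100 app users each, the mean slope was 0.16 and it was significant at the two-sided 5% level in 36% of trials. The size depends on the assumed 0.4: by the same product, correlations of 0.2 each would give 0.04.

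**The case against.** **The analysis is secondary.** The principal strategy, in Mixed-Effect Models, is an intention-to-treat comparison with group, time and their interaction. Engagement does not enter it. A reader might infer that the trial's main result is compromised; the article does not support that. This objection stands and sets the severity.

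**The section gives no equation, and a model with arm and engagement can be fitted.** True. The failure is specific to the interaction, which is what moderation of an arm effect means. The fallback model runs, but it answers a different and confounded question.

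**Controls receive the app later, and the USE questionnaire is not limited to one arm.** Controls may eventually have values. A reader might infer that these must all come after the outcomes, but the article does not date the crossover relative to the 6-month visit, so that cannot be said. Either way, later use is a different exposure from engagement during the comparison. If it began before 6 months, it would also overlap the outcome being compared.

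**The engagement model in App Engagement and Usability already calls itself an association.** Correct. It should not be read as a second instance of the error; it is close to what is needed.

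**The sentence on automatic capture belongs to phase 1.** Also correct. It shows only that engagement is logged inside the app, not how phase 2 controls would be handled.

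**The analysis plan could settle this.** Added detail cannot make these variables usable as plain moderators. The analysis has to be replaced or given explicit causal assumptions, and the article states none.

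**Misreporting is conjecture.** The article does not say it will claim a larger effect in engaged users. The risk lies in the word moderate, not in any stated conclusion.

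**Conclusion.** The concern holds for the Moderation Analysis section. The interaction of arm with engagement or usability is not identified under zero coding or complete-case analysis, and under imputation it is set by the imputation model. That conclusion needs no numerical assumption, only that controls have no app during the comparison, which the article states. The remaining within-arm slope is open to confounding by prognosis and motivation. The 0.16 SD slope and the 36% false-positive rate illustrate this under the assumed 0.4 correlations and are not predictions for this trial. All six listed outcomes are affected, but only in a secondary analysis, so this is a should-fix.

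**What to change.** - In Moderation Analysis, remove engagement and usability as moderators. Restrict moderation of the arm effect to baseline variables collected in both arms, for example baseline PHQ-9, age and sex.
- Report engagement and usability against outcome within the app arm only, adjusted for baseline PHQ-9 and labelled as non-causal association. Place this beside the existing model in App Engagement and Usability.
- Optional, if a causal effect of use is wanted: prespecify an instrumental-variable analysis with assigned arm as the instrument, respecting clinic-level allocation. Use is better entered as a continuous dose than cut at 75% of modules (0.75 × 20 = 15), because a youth who completes 10 to 14 modules also receives content and would strain the exclusion restriction at that cut. State that restriction. Giving phones to both arms helps, since phone receipt is then not a separate pathway.

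**Cost.** A change of wording with no new data. Baseline moderators answer a different question from the one about use. The instrumental-variable estimate would be less precise than a naive comparison, and the plan should say so.
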